### Monitoring of VL

VL will be quantified as the total work performed in each session. Perceived exertion (RPE) will also be considered as a perceptual indicator of internal training load. VL for each session will be calculated as the product of resistance (kg) and the number of repetitions completed. For the ECC+ protocol, additional eccentric contractions will be multiplied by 0.5, as they represent half of the concentric–eccentric contraction cycle. Incomplete contractions that characterize the points of concentric failure (MF_CON_) and eccentric failure (MF_EXC_) will not be included in the calculations.

The RPE will be reported by the participants immediately after each set using the OMNI scale [57]. Additionally, the overall session RPE will be assessed 15 minutes after the end of the session using the same scale, with instructions for participants to evaluate the entire session, not just the last set performed.

### Markers of Neuromuscular Adaptation to Training Protocols

Body composition of both arms will be determined using dual-energy x-ray absorptiometry (DXA; Lunar, iDXA, GE Healthcare) in a supine position. The variable of interest for this study will be the muscle mass of the arm and the entire upper limb of the participants.

The thickness of the biceps brachii and brachialis muscles will be determined at 3 locations, based on percentages of the distance between the posterior margin of the acromion of the scapula and the olecranon of the ulna, namely proximal (50%), middle (60%), and distal (70%) [58], using images obtained by a mode-B ultrasound device (Saevo FP 102, Ribeirão Preto) with a 40 mm linear transducer and a frequency of 10 MHz. Participants will remain in a supine position for 5 minutes before recordings to allow for fluid accommodation. The transducer will be positioned perpendicularly to the skin over the muscle and transversely to the limb. Three images of each assessed region of both muscles will be captured and exported. The ImageJ software (National Institutes of Health) will be used to determine the thickness of each muscle by calculating the difference between the superficial and deep fascias, as well as the total muscle compartment thickness, by calculating the difference between the superficial fascia of the muscle compartment and the osteomuscular interface. Reliability of ultrasound measurements will be carried out by means of the intraclass correlation coefficient.

Muscle function will be evaluated using an isokinetic dynamometer (System 4, Biodex Systems) with participants positioned on a preacher curl bench set at a 45º angle adjusted to the dynamometer. Peak isometric torque and maximum rate of torque development (RTD) will be determined from 2 maximal voluntary isometric contractions of 5 seconds at 2 different angles, 60º and 90º of elbow flexion, with a 1-minute interval between each attempt. After proper positioning on the dynamometer, following the manufacturer’s instructions, and a standardized warm-up (5 minutes of exercise with a self-selected load on a stationary bike followed by 3 submaximal isometric contractions), participants will be instructed to flex the assessed elbow as quickly and with as much force as possible, sustaining the maximal contraction for 5 seconds. A 1-minute rest will be observed between the 2 contractions at each angle. The torque-time curves will be filtered and analyzed in MatLab (Mathworks, IBM), with the highest torque value recorded in the 2 contractions considered as peak isometric torque and the steepest slope of the torque-time curve as RTD. These procedures will be performed for each investigated angle (ie, 60º and 90º of elbow flexion). The contraction with the highest torque value will be used for analysis. Peak torque will be calculated as the highest value on the torque-time curve. The maximum RTD will be calculated as the steepest slope of the torque-time curve. The onset of muscle contraction will be defined as the point where torque values exceed 2.5% of the difference between baseline and peak torque values [59]. For more details on the procedures for filtering and analyzing isometric torque data, refer to [60]. Three minutes after the assessment of isometric strength, dynamic muscle function will be evaluated using nonintercalated maximal isokinetic concentric and eccentric contractions. First, 5 maximal isokinetic concentric contractions of the elbow flexors will be performed with a range of motion of 100° (10º-110º of elbow flexion) at an angular velocity of 60°/s. This range of motion was chosen to allow for greater joint comfort during movement, avoiding full extension at 0º at the beginning of the movement. Additionally, a semipronated grip at 30º is standardized for greater wrist joint comfort. The interval between contractions will be approximately 1.5 seconds, while the dynamometer arm returns passively to the initial position. After a 3-minute recovery interval, 5 maximal isokinetic eccentric contractions of the elbow flexors will be performed with the same range of motion (100°: 10º-110º), angular velocity (–60°/s), and interval between contractions. The highest torque values produced for each contraction will be recorded, and the average of the highest values from the 5 contractions (for each type of contraction) will be calculated and recorded as concentric torque peak and eccentric torque peak.

All data obtained from isokinetic force analyses and ultrasound muscle thickness measurements were performed by an evaluator who was blinded to which protocol each limb performed.

### Statistical Treatment

A formal a priori power analysis was conducted using G*Power software (version 3.1.9.7; Heinrich-Heine-University Düsseldorf). The calculation was based on an effect size of 0.57 [61], for a study that observed significant increases in elbow flexor muscle thickness following resistance training performed to failure, also over a 10-week period. Considering a power (1-β) of .80, a significance α level of .05, and a 2-tailed test for repeated measures (within-subject design), the estimated required sample size was 21 upper limbs. Accordingly, the minimum number of participants needed was 11, assuming each would complete both unilateral protocols. This estimation was based on a 10-week intervention period and informed the recruitment target of this study. The normality of data distribution will be assessed using the Shapiro-Wilk test. Nonparametric data will undergo a logarithmic transformation. The assumptions of homogeneity and sphericity of the data will be checked using Levene and Mauchly tests, respectively. Comparisons over time and between limbs for all dependent variables will be conducted using a 2-way mixed model ANOVA for repeated measures (time effect) and nonrepeated measures (limb effect). If significant effects of limb or time are identified, Bonferroni post hoc adjustments will be applied. Main effect sizes will be calculated and expressed as partial η². If significant interaction effects between limb and time are detected, pairwise comparisons between relevant points will be performed. Effect sizes for significant differences in dependent variables between limbs or over time will be calculated and expressed as Cohen *d*. The significance level adopted will be *P*<.05.

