### Hypotheses

The hypotheses of this study are associated with the specific objectives presented above and are as follows: (1) the total work produced during training sessions will be greater for the intervention involving sets to MF_EXC_; (2) the magnitude of changes in muscle morphological variables will be greater after the intervention involving sets to MF_EXC_; and (3) improvements in muscle function will be more pronounced after the intervention involving sets to MF_EXC_.

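### The sample-size inputs give 27 pairs, not 21, and turning 21 limbs into 11 participants is not valid for the ECC+ versus TRAD comparison

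*Protocol article*

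**What the plan says.** The Statistical Treatment section of the protocol article reports an a priori G*Power calculation. Its inputs are:

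- Effect size: "The calculation was based on an effect size of 0.57 [61". The index is not named.
- Source of the effect size: "for a study that observed significant increases in elbow flexor muscle thickness following resistance training performed to failure".
- Power: "Considering a power (1-β) of .80".
- Significance level: "a significance α level of .05".
- Test: "a 2-tailed test for repeated measures (within-subject design").

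The result is "the estimated required sample size was 21 upper limbs. Accordingly, the minimum number of participants needed was 11", on the assumption that each participant completes both protocols. The section adds that this estimate informed the recruitment target.

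Two other sections fix what has to be powered. Under Experimental Design, each participant trains one arm with TRAD and the other with ECC+. Under Hypotheses, the second hypothesis is that "the magnitude of changes in muscle morphological variables will be greater after the intervention" with sets to eccentric failure. The question is therefore a difference in change between the two arms of the same person.

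**The concern.** All inputs, the result and the conversion to participants are printed, so the calculation can be checked directly. It fails at three places. The number 21 does not follow from the stated two-tailed within-subject test. The step from 21 limbs to 11 participants divides by two, although the sample size of a test comparing the two arms already counts participants. The effect size describes a gain over time, not a difference between two active protocols.

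This is the article's only justification of the sample size, and it presents 11 participants as sufficient for 80% power. If that power is not there, the final results will be interpreted against a sensitivity that the study does not have. The Results section reports 7 completers and further data collection in 2025, so the statement can be corrected before results are reported.

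**Working it through.** **Inputs** (all from Statistical Treatment): effect size 0.57, alpha .05 two-tailed, power .80, within-subject test. *Assumption:* 0.57 is dz, the mean paired difference divided by the SD of the paired differences, because that is the input of a paired test.

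**Formula.** For n pairs, the paired t statistic has n − 1 degrees of freedom and noncentrality δ = dz × √n. Two-tailed power is P(|T| > t(0.975, n − 1)) under the noncentral t distribution. For a one-tailed test, use P(T > t(0.95, n − 1)).

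**Step 1: try to reproduce 21.**

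| Pairs | δ = 0.57√n | Two-tailed power | One-tailed power |
|---|---|---|---|
| 11 | 1.890 | 40.1% | 54.6% |
| 20 | 2.549 | 67.7% | 79.2% |
| 21 | 2.612 | 70.0% | 81.0% |
| 26 | 2.906 | 79.8% | 88.1% |
| 27 | 2.962 | 81.4% | 89.2% |

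The two-tailed requirement is 26.14, so 27 pairs. The one-tailed requirement is 20.45, so 21 pairs. The printed 21 is not reproduced by the stated two-tailed test, but equals the one-tailed answer.

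**Step 2: the conversion to participants.** The article takes 21 / 2 = 10.5 and rounds up to 11. In a paired comparison of ECC+ with TRAD, a pair is one TRAD arm and one ECC+ arm, which is one participant. So 27 pairs means 27 participants (54 limbs), and 11 participants means 11 pairs. Power at 11 pairs is 40.1% two-tailed. With 11 pairs, 80% power needs dz = 0.94 (0.938 before rounding).

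**Step 3: if 0.57 was standardised by the raw SD.** Then dz = 0.57 / √(2(1 − ρ)), where ρ is the correlation between the paired measures. The article gives no ρ, so a range is shown:

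| ρ | dz | Power at 11 pairs | Pairs for 80% |
|---|---|---|---|
| 0 | 0.403 | 23% | 51 |
| 0.5 | 0.570 | 40% | 27 |
| 0.61 | 0.645 | 49% | 21 |
| 0.7 | 0.736 | 60% | 17 |
| 0.8 | 0.901 | 77% | 12 |
| 0.82 | 0.950 | 81% | 11 |

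A correlation of about 0.61 yields 21 pairs, but then 11 pairs have 49% power. A correlation of about 0.82 makes 11 pairs sufficient, but then the requirement is 11 and not 21. No single value supports both printed numbers.

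**Step 4: which quantity 0.57 measures.** The source is described as showing increases in thickness after training to failure, which is a change over time. The hypothesis concerns the extra change with ECC+ over TRAD, and TRAD is itself training to failure. These are different quantities. The extra change may well be smaller than the whole gain, but its standardised size depends on the SD of the between-limb difference, which the article does not give.

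**The case against.** The strongest reply is that the calculation is not shown in full and other settings could have produced 21.

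- **A pre-post calculation.** If 0.57 is a within-limb gain, a limb measured twice is a natural pair and counting limbs makes sense. This stands as a possible account of the unit, and it means that the limb-count fault and the wrong-contrast fault are partly alternative diagnoses. It does not rescue the figure. The two-tailed requirement is still 27, now limbs, which is 14 participants (27 / 2 = 13.5), and such a test does not compare ECC+ with TRAD.
- **A between-factor ANOVA.** Taking 0.57 as Cohen's f, with two groups, two measurements and correlation 0.5, does give 21 (power 81.6%; 20 gives 79.5%). The planned ANOVA does treat limb as a nonrepeated factor. But this setting treats limbs as independent and is not the two-tailed within-subject test that the article states.
- **The one-tailed setting.** A reader might infer from the exact match that a one-tailed test was run. Because other routes reach 21, the document does not prove it.
- **All hypotheses.** A reader might infer that the trial is underpowered for every hypothesis. The document does not support that. The first hypothesis concerns total work, and ECC+ adds repetitions that count towards volume load, so that effect may be large. The 0.57 concerns muscle thickness only and says nothing about power for volume load or torque.
- **The size of the between-protocol effect.** A reader might take it as settled that this effect is below 0.57. It is plausible but not established.

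It is also fair that the article calls 11 a minimum and that recruitment continues, so the final number may be higher. The printed claim that 11 suffices remains wrong.

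**Conclusion.** The point holds. The stated inputs do not give 21, and 11 participants are not shown to give 80% power for the ECC+ versus TRAD difference in change.

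The 40% figure is conditional on reading 0.57 as dz and on treating it as the between-limb effect. Under the raw-SD reading, power at 11 pairs depends on an unstated correlation, and reaching 80% requires one slightly above 0.8. All these figures assume 11 complete pairs. The article's 11 likewise assumes that everyone completes both protocols, so losses would lower power further.

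That 0.57 is a pre-post gain rests on the article's own description of its source, which was not seen.

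**What to change.** In Statistical Treatment:

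1. Replace the power statement with:

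> With 11 participants (11 pairs), a two-sided 5% paired test of the between-limb difference in change in muscle thickness has 80% power for a true difference of 0.94 SD of that difference, and 40% power for 0.57 SD.

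2. Delete the conversion from limbs to participants.
3. Name the effect-size index that 0.57 represents.
4. State that 0.57 came from a pre-post gain and is not an estimate of the ECC+ versus TRAD difference.

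If the final number of participants differs from 11, recompute the two percentages for that number of pairs.

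The cost is wording only. No participants need to be added. The downside is that the stated power becomes less favourable.

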### Experimental Design

The study will be conducted as a within-participant randomized trial. Each participant will undergo 2 different interventions over 10 weeks, each being performed on one of their upper limbs, with 2 training sessions per week separated by a minimum of 48 hours and a maximum of 96 hours. The intervention for each participant’s upper limb will be randomly assigned via electronic randomization. Using commonly available online randomization tools, the first randomization draw will determine whether the left or right upper limb will be selected. Next, the intervention to be applied to the previously selected limb (traditional or ECC+) will be randomly selected. Finally, a randomization draw will decide whether the previously selected protocol and limb will be conducted before or after the unselected protocol (ie, both protocols will be performed in the same session). No counterbalancing based on limb dominance (ie, right-handedness) will be implemented in either the applied protocol or the order of performance. The limb assigned to traditional training (TRAD) will follow a protocol with sets of repetitions until concentric failure (MF_CON_). The limb assigned to the eccentric overload training protocol (ECC+) will follow the same exercise protocol, but with the addition of exclusively eccentric contractions until eccentric failure (MF_EXC_) after reaching MF_CON_.

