The existence of a widely reported cross-education effect, particularly for variables related to muscle function, can be considered a limitation of this design. However, there is a growing trend in strength training research suggesting that, despite this effect, experimental designs comparing active unilateral strength training interventions (ie, with the control limb remaining nonsedentary) performed on each limb of the same individual are more suitable than designs comparing interventions in 2 different groups of people, even if randomized [53]. This is justified by the greater control in such experimental designs over intrinsic factors (eg, gene expression of protein transcription factors, muscle fiber type distribution, and capillary-to-fiber ratio) and extrinsic factors (eg, sleep quality, training level, and diet), which are known to influence responses to strength training and cannot be controlled in designs involving different individuals in groups. Furthermore, when the primary outcome of the investigation is muscle hypertrophy, the unilateral training design appears even more suitable, as there is evidence that there is no cross-education effect for this type of outcome [54-56].

Neuromuscular function and body composition markers will be collected 1 week before and 1 week after the interventions and compared between limbs. The VL performed in each training session and the session’s perceived effort will be recorded for comparison over time and between limbs. The experimental design of the study is illustrated in Figure 1.

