## Discussion

### Anticipated Findings

The objectives of this study are to compare, through a randomized intraparticipant trial, the chronic effects of RT sets performed up to MF_EXC_, after MF_CON_, in relation to series performed only up to MF_CON_ on the VL produced during the training sessions, muscle mass, muscle thickness of the proximal, medial and distal regions of the arm, and muscle function assessed by maximum isometric, concentric, and eccentric strength. The hypotheses are that (1) the total work performed during the sessions will be greater in the sets performed up to MF_EXC_, (2) the muscle morphological adaptations will be more pronounced after the intervention with sets up to MF_EXC_, and (3) the improvements in muscle function will also be more pronounced with the ECC+ protocol. If the hypotheses that a greater training volume induces greater hypertrophy adaptations are confirmed, the results will align with previous findings in the literature [2,6,29,31]. If so, the proposed intervention could be implemented as a new practical method in the personal trainer’s professional context, providing session time efficiency (ie, increased training density), as the volume load could be substantially increased with sets taken to MF_EXC_, thereby inducing greater responses. Regarding regional hypertrophy, the analysis of the 3 regions (50%, 60%, and 70% of the arm length) may indicate that the thickness response is different between the studied protocols. Studies indicate that hypertrophy may occur nonuniformly throughout the muscle, being more pronounced in the regions that undergo greater stretching during the exercise [62]. In the preacher curl bench exercise, used in this study, peak torque occurs at the beginning of the concentric phase and at the end of the eccentric phase, which maximizes stress on the distal portion of the biceps brachii when stretching and suggests that exercise biomechanics plays a crucial role in regional hypertrophy [63]. Some possible limitations could be that the fatigue and muscle damage induced by the ECC+ protocol may not maximize hypertrophic responses, even with a higher volume load [64,65]. Another limitation is the choice to use this method on fusiform muscles, making it impossible to analyze pennation angle, which could be altered with greater emphasis on eccentric contractions, as well as not measuring fascicle length, which could be carried out in future work using the ECC+ method in other pennate muscles. The reason for choosing to investigate the elbow flexor muscles was exclusively related to the implementation logistics and the availability of equipment in our laboratory. However, as the study does not aim to answer questions related to kinesiological variables but rather to the manipulation of training variables, such as hypertrophy and strength, it is likely that this choice will not significantly interfere with the main outcome. Additionally, the unequal volume load between limbs could be considered a limitation of the protocol. However, this choice was made to ensure greater ecological validity. The participants’ uncontrolled diet, particularly in terms of carbohydrate and protein intake, is also considered a limitation. Although the study uses a within-subject design, this factor could still restrict training responses. Finally, another limitation of the present protocol concerns the absence of counterbalancing based on upper limb dominance. Although randomization was applied to the selection of the limb, the intervention (TRAD or ECC+), and the order of execution, no specific control was implemented to ensure that either the dominant or nondominant arm would perform a given protocol or initiate the session. This decision aimed to preserve the simplicity and feasibility of the protocol’s practical application. Although lateral dominance may influence muscular performance, such an effect could potentially be minimized if, in this study, 10RM testing reveals similar strength values between participants’ right and left upper limbs. This equivalence would suggest that, at least from an initial functional standpoint, dominance may not have a relevant impact on strength capacity. Nevertheless, the literature indicates that dominance can affect neuromuscular performance due to factors such as motor learning, neural recruitment, and habitual use. Therefore, we acknowledge that subtle dominance-related differences may exist and contribute to variability in training responses. As such, researchers applying this protocol are encouraged to consider including dominance as a covariate or to investigate its influence in future analyses, particularly in studies with greater statistical power.

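### ECC+ versus TRAD is tested by an unadjusted change-score contrast although each limb's pre-training value is collected; the test is valid, but prespecified baseline adjustment would be a cheap, conditional improvement

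*Protocol article*

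**What the plan says.** Experimental Design in the protocol article sets out the comparison: "The study will be conducted as a within-participant randomized trial". One arm receives each protocol, and the arm is chosen by a random draw. On measurement it says: "Neuromuscular function and body composition markers will be collected 1 week before and 1 week after the interventions and compared between limbs". The section on markers of adaptation confirms that both sides are assessed, for example: "Body composition of both arms will be determined using dual-energy x-ray absorptiometry". Each of these outcomes therefore has one pre-training and one post-training value per limb.

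Statistical Treatment names a single model: "Comparisons over time and between limbs for all dependent variables will be conducted using a 2-way mixed model ANOVA". Its two factors are described as "repeated measures (time effect) and nonrepeated measures (limb effect". The pre-training value enters only as a level of time. The follow-up step is also unadjusted: "If significant interaction effects between limb and time are detected, pairwise comparisons between relevant points will be performed". The abstract likewise names only a 2-way ANOVA.

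Nothing in the design balances the arms at baseline: "No counterbalancing based on limb dominance (ie, right-handedness) will be implemented in either the applied protocol or the order of performance". The one covariate mentioned is in the discussion, and it is advice to others rather than part of this plan: "researchers applying this protocol are encouraged to consider including dominance as a covariate".

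**The concern.** Hypotheses 2 and 3 predict larger morphological and functional gains with ECC+. In the stated model the limb-by-time interaction tests them. With two time points, that interaction subtracts the whole baseline difference between a woman's arms from the post-training difference. If the two differences are imperfectly correlated, subtracting all of it is too much. When the TRAD arms happen to start higher, the estimate leans towards ECC+; when the ECC+ arms start higher, it leans towards TRAD.

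An adjusted analysis estimates how much of the baseline difference to subtract. Because arms are randomised, the expected baseline difference is zero, so adjusting for it is legitimate. With about 11 women and no balancing by dominance, some chance difference between arms is to be expected, and the data needed to handle it are already being collected. At stake are some precision and a more stable answer for the arms actually drawn. The validity of the test is not at stake. Volume load is outside this point.

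**Working it through.** **Inputs.** From Statistical Treatment: minimum 11 participants, effect size 0.57, two-tailed alpha .05. The article does not say how 0.57 is standardised; here it is assumed to be the mean ECC+ minus TRAD difference in change, divided by its SD. The article gives no rho, so a range is used. Pre and post limb differences are assumed normal with equal SD, set to 1. Limbs are assumed to be analysed as paired.

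**The plan's own figure.** The article gives no figure for baseline adjustment. Its sample-size figure (21 limbs, taken as 11 women) is not reproduced by a two-tailed paired test at 0.57, which has power 0.40 with 11 pairs and 0.70 with 21, and needs 27 pairs for 0.80. That is a separate matter; only the 40% starting point is used here.

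**1. Equivalence.** For each woman let A = pre-training difference and B = post-training difference, both ECC+ minus TRAD. The interaction contrast is (ECC+ post − ECC+ pre) − (TRAD post − TRAD pre) = B − A. The estimate is the mean of B − A whether limbs are treated as independent or paired; only its standard error differs.

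**2. Large-sample variance.** Change score: Var(B − A) = 2(1 − rho). Adjusted: residual variance 1 − rho². Ratio, adjusted to change score: (1 − rho²) / [2(1 − rho)] = (1 + rho)/2. This is 0.65 at rho 0.3, 0.75 at 0.5, 0.85 at 0.7, 0.90 at 0.8 and 0.95 at 0.9.

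**3. Cost of estimating the slope with 11 pairs.** The variance of the intercept is inflated by 1 + 1/(n − 3) = 1 + 1/8 = 1.125.
- rho 0.3: 0.65 × 1.125 = 0.73
- rho 0.5: 0.75 × 1.125 = 0.84
- rho 0.7: 0.85 × 1.125 = 0.96
- rho 0.8: 0.90 × 1.125 = 1.01
- rho 0.9: 0.95 × 1.125 = 1.07

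Break-even: (1 + rho)/2 = 1/1.125 = 0.889, so rho = 0.78.

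**4. Simulated power, 11 women.** The post-training effect is set to 0.57 × √[2(1 − rho)], so the paired change difference has standardised size 0.57 at every rho.

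| rho | change score | baseline-adjusted |
|---|---|---|
| 0.3 | 40–41% | 51–52% |
| 0.5 | 40% | 46% |
| 0.7 | 40% | 42% |
| 0.8 | 40% | 40% |
| 0.9 | 40% | 38% |

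Type I error is about 5% for both methods.

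**5. Conditional over-correction.** If the mean of A happens to equal b, the expected change-score estimate is the true effect − (1 − rho)b. At rho 0.5, a one-standard-error imbalance is b = 1/√11 = 0.30, and the shift is 0.5 × 0.30 = 0.15. At that rho the SD of B − A is √[2 × 0.5] = 1, so the effect is 0.57 and the shift is 0.15/0.57 = 26% of it. The standard error of the change-score estimate is also 1/√11 = 0.30, so the shift is half a standard error.

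**6. Where the intercept is taken.** If A is centred at its sample mean, the intercept becomes the raw mean of B, with no adjustment and too small a standard error. Simulated type I error at 11 women is then 8% at rho 0.5, 14% at 0.7, 21% at 0.8 and 35% at 0.9. With A uncentred it stays at 5%.

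**The case against.** The strongest reply is that nothing is broken. Arms are randomised, the change score is unbiased over randomisation, its type I error is nominal, and it directly tests what the hypotheses state. All of that stands. A reader might infer from the conditional shift that the planned test is biased. The documents do not support that: the 26% figure applies to one particular imbalance at one assumed rho, equals half a standard error, and is already contained in the test's standard error and its 40% power.

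A second reply is that the gain is unknown. This also stands. No correlation is reported, so it cannot be said that adjustment will usually raise power here. The relevant rho is that of the within-woman limb difference. It should be lower than the raw pre-post correlation, because stable differences between women cancel, but nothing in the article places it below 0.78. Nor does adjustment fully remove the effect of a chance imbalance: with 11 pairs at rho 0.5, the simulated 95% range of the estimated slope is about −0.1 to 1.1.

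A third reply is that 40% belongs to a paired test, whereas the model as written treats limb as nonrepeated. That is correct. Every figure here describes a further step after pairing is restored. In simulations over assumed correlations, ignoring the pairing cost more power than leaving out the baseline.

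A fourth reply is that seven women have finished and Table 1 schedules analysis from late 2024, so the change comes mid-trial. This limits how it should be made but does not rule it out: no data are added, and the rule can be fixed before the final analysis.

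**Conclusion.** The point holds as a recommended improvement to a method the article itself fixes. It is not an error that invalidates the test. For outcomes with a pre-training value in each limb, the ECC+ versus TRAD test is an unadjusted change-score comparison: valid on average, but over-correcting by (1 − rho) times any chance baseline limb difference in the arms drawn.

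At 11 women the effect of adjusting ranges from about 11 points of power gained at rho 0.3, through 6 at 0.5 and 1 to 2 at 0.7, to nothing near 0.78 and about 2 points lost at 0.9. This rests on 0.57 as the standardised paired change difference, equal pre and post SDs, normality and paired limbs. Power stays low in every case, so adjustment does not cure the sample size. The nonrepeated limb factor and the sample-size figure are separate issues.

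**What to change.** Once limbs are treated as paired, add to Statistical Treatment, for each outcome with a pre-training value: the within-woman post-training difference (ECC+ minus TRAD) will be regressed on the within-woman pre-training difference, entered uncentred and not mean-centred, and the intercept, which is the protocol effect at zero baseline difference, will be reported with its 95% CI. Keep the within-limb pre-to-post changes as a description of each protocol.

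The cost is a sentence or two of text, one degree of freedom and an imprecisely estimated slope at this sample size; no participants or measurements are added. Date the change, make it before the final analysis, and state whether any ECC+ versus TRAD results had been seen by then.
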